#### Planned data analysis

##### Descriptive analysis

Data analysis will address our main hypothesis that parents who engage in the training will exhibit improved communication about potential hazard detection with their teens compared to those in the control condition. All analyses will include covariates of relevant demographic (e.g., sex, race/ethnicity) and driving related covariates (e.g., driver education engagement, duration of licensure, family communication patterns, etc.). P-value adjustments will be made as necessary.

##### Primary analysis

The primary set of analyses will examine the impact of the intervention on real-time parental instruction surrounding hazard identification and mitigation separately for the simulator and naturalistic drives.

**Simulator drives** Generalized linear mixed models will be used to predict conversational measures using a fixed effect of condition and covariates detailed above. For presence/absence measures (e.g., hazard anticipation communication), the probability of occurrence will be modeled using a mixed-effects logistic regression modeling approach. Condition will be included as a fixed effect, along with relevant demographic and driving covariates. Potential random effects of participant and hazard scenario will be determined using loglikelihood ratio testing. Outcomes will be interpreted as probability of occurrence. For count measures (e.g., functional driving instruction), the frequency of occurrence will be modeled using a mixed-effects position regression approach. Again, condition will be included as a fixed effect, along with relevant demographic and driving covariates and random effects structure determined with loglikelihood testing. Outcomes will be interpreted as incident rate ratios. Additionally, we will examine the distributions of teen temperament, family communication pattern, and parenting style and explore if intervention differences are suggested. P-value adjustments for multiple tests will be undertaken. We predicted that parents in the intervention arm of the study will exhibit increased probability and incidence of higher-order instruction of hazard anticipation and response with their teen.

**Naturalistic drives** The rate for each conversational outcome per 10 min of naturalistic driving will be modeled using a mixed-effects Poisson regression. The log of drive duration in 10-minute units will be included as an offset term to account for variation in drive length, such that model coefficients reflect expected counts per 10-miunte interval, rather than per drive. As with simulated driving, condition will be included as a fixed effect along with demographic and driving covariates. A random intercept of dyad will also be included to account for the correlation among the repeated drives within dyad. Drive number (1–4) will also be explored as a potential covariate to account for potential change over the naturalistic driving period.

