**Methods:**

Teen drivers in the learner phase of licensure (ages 14 to 17) and their parents were recruited via email listservs, postings and flyers to area schools, social media postings, and word of mouth. Pending eligibility screening and consent, dyads were randomly assigned to either the intervention or control arm of the study. Parents in the intervention arm of the study engaged in an online training program that sought to help parents better communicate their expert hazard anticipation knowledge to their teens. The training was two-fold: parents engaged in a web-based program that provided insights on how to best communicate with their teen when encountering hazards on the roadway, followed by a guided joint task that allowed parents to practice these skills with their teen in a safe environment by watching videos of hazards unfold. The study took place over two study visits approximately 4 weeks apart. At Visit 1, parents and teen completed questionnaires and engaged in an acclimation drive to ensure dyads would not experience motion sickness in simulated driving. All participants were then given a dashcam to record four naturalistic driving sessions before returning for Visit 2 where participants completed a study drive with 17 embedded hazards. Driving sessions (simulated and naturalistic) will be coded for content to determine intervention efficacy for improving parental instruction. Primary outcomes will include parental use of functional driving instructions, hazard identification, hazard anticipation communications, if these communications occurred before hazards become critical and if they contain elements of motivational interviewing, which were modeled in the web-based program. Secondary outcomes of teens’ driving performance will include hard braking events and lane changes in response to hazards and parental instructions.

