### Study population

The HazAPP RCT study enrolled 103 parent-teen dyads, of which 102 completed all study procedures. One dyad chose to withdraw from the study due to the parent experiencing motion sickness in the simulator at Visit 1. Teen age ranged from 14 to 17 years old, with 52 males and 50 females. Each teen participated with one parent or legal guardian. An even gender balance was achieved via sex-stratified randomization, given higher crash rates observed among male teen drivers (IIHS [4]), . Otherwise, participants were selected without regard to race, ethnicity, and other socioeconomic factors.

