#### Randomization

Randomization was stratified by sex (male and female) to account for the substantially higher fatal crash rates observed among male teen drivers (e.g., IIHS [4]), , ensuring balanced representation across study arms and allowing sex to be included as a covariate in planned analyses. Prior to participant enrollment, two blocks of participant IDs were created. One block was for females, the other for males. Half of the IDs in each block indicated control condition assignment, while the remaining half indicated assignment to the intervention condition. These blocks were then entered into a list randomizer. Condition assignment strictly adhered to the randomly ordered list. Random assignment occurred after consent was complete.

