### Study measures

#### Primary outcomes

The primary study outcomes will be derived from the variables coded (Table 4) using recorded conversations that parents and teens had when engaging in the simulator and naturalistic drives.

Once reliable, study team members will code whether parents identify the hazard, whether the parent verbally identifies roadway hazards, if hazard identification uses a hazard anticipation communication (i.e., higher-order communication), if instruction precedes or follows the hazard event, if the hazard anticipation communication includes elements of motivational interviewing, and how many times parents provide functional driving instructions. Hazard anticipation communication, a form of higher-order driving instruction that can be applied more generally to driving (e.g., “When there are brake lights ahead, you should be ready to brake too.”), will be coded when parents indicate why the hazard is dangerous by causally connecting dangerous features and their potential outcomes. Functional instruction will be coded for instruction that applies only to the current context (e.g., “Slow down.”). We will also code whether the teen verbally identifies the hazard via hazard anticipation communication or by only pointing out the hazard and if identification precedes or follows the hazard event. Measures will be captured for each hazard that is presented in the simulator drive for a total of 17 repeated measures per dyad. For each of the 17 scenarios embedded in the simulator drive, a binary indicator reflecting presence or absence will coded for hazard anticipation communication, its sub codes, and hazard identification only. The number of functional driving instructions produced by the parent per hazard scenario will be recorded as a count.

Unlike simulator drives, hazards encountered in during naturalistic driving are not standardized. Therefore, coding will focus on general hazard anticipation patterns rather than per-hazard responses. Raw counts of each conversational measure will be recorded. because drives varied in length (10–30 min), counts will be modeled as a rate per 10 min of drive time. Each dyad contributed four naturalistic drives.

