##### Secondary analysis

The secondary set of analyses will examine any changes to teen’s driving behavior in response to parental instruction during the simulator drive. More specifically, we will use mixed-effects models to predict outcomes of risky driving behaviors and lane changes. Each model will include a fixed effect of condition and covariates detailed above. Potential random effects of participant and hazard scenario will be determined using loglikelihood ratio testing. P-value adjustments for multiple tests will be undertaken. We expected that teens of parents in the intervention arm of the study will exhibit improved driving responses to potential hazards in the simulator drive.

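### A likelihood ratio test decides whether the dyad random intercept stays in the simulator models, although the dyad is the unit of randomisation; it should be kept by design

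*Protocol article*

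**What the plan says.** The abstract's Methods paragraph gives the unit of allocation: "dyads were randomly assigned to either the intervention or control arm of the study". Under Primary outcomes the simulator data are repeated within that unit: "Measures will be captured for each hazard that is presented in the simulator drive for a total of 17 repeated measures per dyad".

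Under Primary analysis, the Simulator drives paragraph sets the rule for the mixed-effects logistic models: "Potential random effects of participant and hazard scenario will be determined using loglikelihood ratio testing". For the count models it says "random effects structure determined with loglikelihood testing". Under Secondary analysis, "we will use mixed-effects models to predict outcomes of risky driving behaviors and lane changes", and the sentence on potential random effects is repeated there.

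The Naturalistic drives paragraph, also under Primary analysis, takes a different line: "A random intercept of dyad will also be included to account for the correlation among the repeated drives within dyad". No test is attached to that term.

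**The concern.** Condition is a between-dyad factor, so its standard error has to carry the between-dyad variation. The clustering follows from the design and does not need to be discovered in the data. The simulator rule nevertheless makes the dyad effect optional, outcome by outcome. A test of a variance component has little power when the outcome is rare, the clustering weak or the records per dyad few, so failing to reject says little. If the term is dropped while the true variance is above zero, the condition effect looks more precise than it is.

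Calling the models mixed-effects does not protect against this, because a model with only a hazard-scenario effect also fits that label. The reason given for the naturalistic intercept, correlation within dyad, applies equally to 17 hazards met by the same parent and teen. What is at stake is the type I error of the condition test in the primary and secondary simulator analyses.

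**Working it through.** **Inputs from the Protocol article.** "The HazAPP RCT study enrolled 103 parent-teen dyads, of which 102 completed all study procedures" (Study population). Allocation is equal within sex blocks: "Half of the IDs in each block indicated control condition assignment, while the remaining half indicated assignment to the intervention condition" (Randomization). Each dyad has 17 simulator records, so 102 × 17 = 1,734 in all. In Table 4, the before-hazard and motivational-interviewing sub-codes are conditional on hazard anticipation communication (HAC) being present.

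**Assumptions.** The article gives no event rates, intraclass correlation (ICC) or alpha. I take a two-sided 5% level, 51 dyads per arm and a between-dyad SD σ of 0 to 1.0 on the logit scale. The latent ICC is σ²/(σ² + 3.29), so it runs from 0 to 0.23. The article states no figure on this point that could be reproduced.

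**Step 1: if the dyad effect is left out.** Design effect = 1 + (17 − 1) × ICC, with ICC on the observed 0/1 scale. True level of a nominal 5% test = 2 × [1 − Φ(1.96/√design effect)].

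| ICC | Design effect | True level |
|---|---|---|
| 0.01 | 1.16 | 6.9% |
| 0.02 | 1.32 | 8.8% |
| 0.05 | 1.80 | 14.4% |
| 0.10 | 2.60 | 22.4% |

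These apply only when the term is actually dropped, and the test seldom drops a large effect. The two parts must be combined.

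**Step 2: the two-step rule.** Data were simulated with no condition effect and no scenario effect, 3,000 runs per setting. A random-intercept logistic model was compared with plain logistic regression by likelihood ratio test (chi-square, 1 df, 5%), and condition was tested in the model selected. Selected settings:

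| Records per dyad | Event probability | Latent ICC | Dropped | Level, two-step rule | Level, always kept | Level in runs where dropped |
|---|---|---|---|---|---|---|
| 17 | 0.3 | 0.027 | 55% | 6.6% | 5.5% | 8.8% |
| 17 | 0.3 | 0.046 | 16% | 6.4% | 5.8% | 12.5% |
| 17 | 0.3 | 0.13 | 0% | 5.8% | 5.8% | none dropped |
| 17 | 0.1 | 0.046 | 68% | 6.4% | 5.2% | 7.6% |
| 17 | 0.1 | 0.071 | 39% | 6.6% | 5.8% | 9.5% |
| 17 | 0.1 | 0.13 | 3% | 5.6% | 5.6% | 16.9% |
| about 3.4 | 0.3 | 0.071 | 84% | 6.3% | 5.3% | 7.1% |
| about 3.4 | 0.3 | 0.13 | 56% | 7.1% | 6.1% | 9.1% |
| about 3.4 | 0.3 | 0.233 | 16% | 5.7% | 5.1% | 9.3% |

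The rows with 3.4 records (17 × 0.2) represent sub-codes analysed only where HAC occurred. The Monte Carlo standard error of one level near 6% is √(0.06 × 0.94/3000) = 0.4 points. Both procedures were run on the same simulated data.

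A separate simulation (700 to 1,500 runs per setting, Monte Carlo error about 1 point) used rarer or sparser outcomes:
- 5% prevalence, σ = 0.6: dropped in 52%; overall 6.2% against 4.8% with the intercept kept.
- 3% prevalence, σ = 0.8: dropped in 38%; overall 7.4% against 6.3%.
- About 3 usable scenarios per dyad, σ = 0.9: dropped in 34%; overall 6.6% against 5.3%.

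Across both simulations the overall excess is at most 1.4 points.

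**Step 3: how much of the error in the dropped runs comes from dropping.** Where the intercept is kept, the two procedures are identical. In the dropped runs, therefore, level with the intercept kept = level when dropped − (overall two-step level − overall kept level)/proportion dropped.
- 17 records, event probability 0.3, ICC 0.027: 8.8 − 1.1/0.547 = 6.8%.
- About 3.4 records, event probability 0.3, ICC 0.13: 9.1 − 1.0/0.558 = 7.3%.
- 5% prevalence (level when dropped 8.3%): 8.3 − 1.4/0.52 = 5.6%.
- 3% prevalence (12.5%): 12.5 − 1.1/0.38 = 9.6%.
- About 3 usable scenarios (10.4%): 10.4 − 1.3/0.34 = 6.6%.

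In these settings dropping the term adds about 2 to 4 points within the affected runs. The rest of the distance from 5% would be there with the intercept retained.

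**The case against.** The strongest reply is that the rule does little damage. With 102 dyads and 17 records each, the test almost always keeps a dyad effect large enough to matter. A parent's habitual way of instructing may well cluster strongly, and then the main HAC outcome is barely touched. That stands, and it limits the size of the point.

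A reader might infer that the condition tests would run at 8 to 12% error. The simulations do not support that as a figure for the plan: those rates belong only to runs in which the term was dropped, and Step 3 shows that dropping causes only part of them.

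A reader might also infer that all 1,734 records would be treated as independent. That follows only if the hazard-scenario effect is dropped too, and the plan tests both. A model with scenario alone would still leave out the between-dyad variation that the condition test needs.

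Other limits also stand. The simulations are logistic and have no scenario effect, so they give no magnitude for functional instructions or risky driving events, which are counts. The article does not say which outcomes will be rare. Primary outcomes can be read as coding the sub-codes for all 17 scenarios, while Table 4 supports the sparser reading. No reference distribution is named for the likelihood ratio test; with a 50:50 mixture reference the term is dropped less often (44% rather than 55% at ICC 0.027, event probability 0.3).

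Finally, the simulator data are crossed (dyad by scenario) and the naturalistic data are nested, so some difference in model structure is reasonable. That can justify testing a scenario term. It does not justify making the dyad term optional. Nor can this be put down to detail left to another document, because the article states the rule.

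**Conclusion.** The point holds, with modest size. As written, the simulator models allow the randomised unit to leave the model on a non-significant test, whereas the naturalistic models do not. For binary outcomes the overall type I error of the two-step rule is about 6 to 7% at worst (7.4% the highest seen), roughly 1 point above the level with the intercept always kept. The exposure is concentrated in rare outcomes, weak clustering and HAC-conditional sub-codes, and is negligible for common, strongly clustered outcomes. The mechanism is certain. The magnitude rests on assumed event rates, ICCs and alpha, and for the count outcomes it was not estimated. The text does not show an intention to ignore clustering, only a rule that fails to protect against it.

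**What to change.** In the Protocol article, change the logistic-model sentence and the separate count-model sentence under Primary analysis (Simulator drives), and the matching sentence under Secondary analysis, to this effect: every simulator model includes a random intercept for dyad regardless of its significance; likelihood ratio testing is used only for additional terms, such as a hazard-scenario effect; if a model does not converge, the other terms are simplified first, or dyad-clustered robust standard errors are used for condition. The scenario intercept need not be forced in to cure this defect, since every dyad meets the same 17 scenarios and scenario is therefore crossed with condition.

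Write dyad in place of participant, because the Sample size section counts two participants per dyad.

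The cost is one sentence in three places, with no new data. Keeping the intercept when there is truly no clustering costs little: the simulated level was then 4.3 to 5.0%. The article describes coding and modelling as still to come, so the rule can be settled before any model is fitted.

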### Objectives

The objective of the parallel randomized trial (ClinicalTrials.gov: NCT06611241) is to evaluate the feasibility of a parent-focused intervention, the Hazard Anticipation Program for Parents (HazAPP). HazAPP seeks to improve parental instruction of novice teen drivers’ hazard anticipation skills. We used driving simulation to test the feasibility of the parent-focused intervention by comparing parent instruction between dyads whose parents were randomly assigned to the intervention compared to those that were randomly assigned to the control condition. We hypothesize that parents in the intervention arm of the study will exhibit increased use of hazard anticipation instruction and will be more likely to do so before a hazard becomes critical.

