**Primary Outcomes**			
Hazard Anticipation Communication (HAC)	Higher-order communication that helps drivers identify and respond hazards by pointing out why they are critical and the clues on the roadway you can use to identify them. (e.g., “There could be something in front of the bus that we can’t see. They could pop out without warning.”)	Presence/Absence	Count
Before hazard	If HAC is present, does the HAC occur before or after the hazard would become critical if no action were taken	Presence/Absence	Count
Motivational interviewing	If HAC is present, are elements of motivational interviewing present in parent’s HAC?	Presence/Absence	Count
Functional Driving Instruction	Driving instruction related to vehicle handling and navigation (e.g., “Slow down.”, “Check your speed.”)	Count	Count
Hazard Identification Only	Identification of the hazard without any additional context or instruction (e.g., “I see a pedestrian.”, “That car is braking.”)	Presence/Absence	Count

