## Discussion

The Hazard Anticipation Program for Parents (HazAPP) was developed to improve teens’ hazard anticipation skills by providing parents with the needed tools to provide real-time hazard anticipation instruction to their teen in the learner phase of licensure. The current RCT seeks to evaluate the feasibility of a web-based program, HazAPP, and determine its ability to shift parents from reactive, functional instruction toward proactive hazard anticipation communication.

HazAPP is an innovative approach to improving teens’ hazard anticipation skill because it goes beyond existing systems of teen driver education to specifically train parents to teach teens in hazard anticipation – the leading cause of teen motor-vehicle crashes [5, 24, 25]. HazAPP also fills an important gap in teen crash prevention because there are currently no programs available for supporting parent instruction of roadway hazards. Additionally, HazAPP’s web-based design is highly accessible, making the program ideal for all families, including those who may lack access to other driving resources.

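### In the naturalistic drives, before-hazard HAC is analysed only as a rate per 10 minutes, which cannot separate earlier timing from more HAC

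*Protocol article*

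**What the plan says.** The Objectives section of the protocol article states a hypothesis in two parts. Intervention parents will use more hazard anticipation instruction, and they "will be more likely to do so before a hazard becomes critical".

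Table 4 lists the before-hazard code under the primary outcomes and defines it as an attribute of HAC: "If HAC is present, does the HAC occur before or after the hazard would become critical if no action were taken". In the naturalistic drives this code is a count. The Primary outcomes section under Study measures adds that raw counts will be recorded and modelled per 10 minutes of driving.

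The Primary analysis section, under Naturalistic drives, applies one model to all these measures: "The rate for each conversational outcome per 10 min of naturalistic driving will be modeled using a mixed-effects Poisson regression". The denominator is driving time: "The log of drive duration in 10-minute units will be included as an offset term to account for variation in drive length", so that "model coefficients reflect expected counts per 10-miunte interval, rather than per drive". Condition is the fixed effect, with demographic and driving covariates and a random intercept for dyad. Nowhere does the article make the HAC count an offset, a covariate or a comparison row.

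**The concern.** The definition in Table 4 asks, of a HAC that was given, whether it came before or after the critical point. The planned naturalistic model asks how many before-hazard HACs occur per 10 minutes. These questions have the same answer only if the arms give the same total amount of HAC, yet the programme is meant to raise that total.

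If parents simply talk more about hazards, with the same split between before and after, the before-hazard rate rises in step. The result then largely repeats the HAC result. It tells the reader that more advance warnings were given, but not that warnings came earlier. The conditional reading of the timing hypothesis therefore has no separate test in these drives.

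**Working it through.** **Algebra.** Let V be the intervention/control ratio of total HAC per 10 minutes, and let s0 and s1 be the shares of HAC given before the hazard in the control and intervention arms.

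- Before-hazard rate ratio (the planned coefficient, exponentiated) = V × s1/s0.
- After-hazard rate ratio = V × (1 − s1)/(1 − s0).
- Ratio of the two = [s1/(1 − s1)] / [s0/(1 − s0)]. V cancels, so this ratio depends on timing only.

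With s0 = s1 = 0.5 and V = 1.5, the before and after rate ratios are both 1.5, and their ratio is 1.0. The planned test responds although timing is unchanged.

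**Inputs from the article.** 102 dyads completed, with half of the IDs in each sex block assigned to each arm (simulated as 51 per arm). Each dyad contributes four drives of 10–30 minutes (simulated as uniform).

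**Assumed, because the article gives no values.** Control HAC rate 0.25–2 per 10 minutes; between-dyad SD of the log rate 0.5, 0.7 or 1.0; between-dyad SD of the logit share 0.5; before-share 50% in both arms unless stated; two-sided 0.05 without multiplicity adjustment. There is no figure in the plan on this point to reproduce.

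**Simulation.** There were 600 trials per setting. Each trial fitted a Poisson model to dyad totals with log-duration offset and robust variance, standing in for the mixed model. Percentage of trials in which the before-hazard rate test is significant, with timing unchanged:

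| Dyad SD | Control rates per 10 min | HAC ×1 | HAC ×1.5 | HAC ×2 |
|---|---|---|---|---|
| 0.5 | 0.5, 1, 2 | 5.5–8.8 | 70–87 | 99–100 |
| 0.7 | 0.25, 0.5, 1, 2 | 5–7 | 45–69 | 88–97 |
| 1.0 | 0.5, 1, 2 | 5.5–8.5 | 38–41 | 76–79 |

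The ×1 column is close to nominal, so the planned test behaves properly for its own null. Two analyses that isolate timing stay near nominal whatever the volume. A before/after-by-condition contrast clustered on dyad (SD 0.7) is significant in 5–7% of trials. A model with log HAC count as offset (SD 0.5 and 1.0) is significant in about 4–9%, with an estimated ratio of about 1.00.

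**When timing and volume both vary:**

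| Share before | V | Before-hazard rate ratio by formula | Planned test | Ratio of rate ratios |
|---|---|---|---|---|
| 40% → 60% | 1 | 1 × 0.6/0.4 = 1.50 | simulated 1.48, significant in 75% | 2.25 |
| 60% → 40% | 2 | 2 × 0.4/0.6 = 1.33 | simulated 1.36, significant in 56% | 0.44 |
| 40% → 60% | 2/3 | 2/3 × 0.6/0.4 = 1.00 | simulated 0.98, significant in 7% | 2.25 |
| 50% → 70% | 0.5/0.7 = 0.71 | 1.00 | significant in 4–7% | 2.33 |

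The first three rows use a control rate of 1 and SD 0.5; the last uses control rates of 0.5 and 1 and SD 0.7. In the last row the before/after contrast is significant in 94–99% of trials. Simulated ratios differ slightly from the formula because shares vary between dyads. The planned test does pick up a pure timing shift at constant volume (first row). It fails to identify timing once volume moves too.

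**The case against.** The strongest reply is that the rate is a legitimate quantity. It is a direct randomised comparison, the article states correctly what its coefficient means, and more advance warnings per 10 minutes may be what matters to a learner. The phrase about being more likely to instruct before the critical point can also be read unconditionally, and the planned rate answers that reading. All of this stands, and it is why the rate should stay.

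It also stands that the hypothesis is tied mainly to the simulator. Objectives introduces it directly after describing the simulator comparison, and Naturalistic drive capture presents the dashcam recordings as supplementary. Even so, Study measures and Primary analysis place the naturalistic measures within the primary outcomes.

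The programme teaches parents to discuss hazards both in advance and afterwards, so it could succeed with an unchanged share. That limits what a null contrast would mean, but it does not make the rate a measure of timing.

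A reader might infer more than the article supports:

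- *That a higher rate will be reported as earlier instruction.* The article never says so.
- *That the 40–100% are false positives.* They are power to detect a real rise in before-hazard HAC.
- *That motivational interviewing has the same defect.* The arithmetic is the same, since Table 4 asks "If HAC is present, are elements of motivational interviewing present in parent’s HAC", but Objectives states no hypothesis about style.
- *That the Discussion's aim to "shift parents from reactive, functional instruction toward proactive hazard anticipation communication" supports the point.* That passage contrasts functional instruction with HAC, not HAC before with HAC after the critical point, and separate outcomes cover it.

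Nor can this be put down to detail left to an analysis plan. The article fixes the model, the offset, the effect of interest and its meaning for every naturalistic outcome.

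**Conclusion.** The point holds in a limited form. The planned before-hazard rate ratio is volume ratio times share ratio. It is valid for the amount of before-hazard HAC but does not, on its own, test whether HAC comes earlier given that it occurs. This follows from the definitions and needs no assumed rate.

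The size does depend on assumptions. With an equal 50% share, a 1.5-fold rise in HAC makes the test significant in 38–87% of trials and a doubling in 76–100%, over the rates and SDs listed. Multiplicity adjustment, which the article mentions, would lower these figures. The cases in which a real timing gain is missed require total HAC to fall by about 29–33%, against the direction hypothesised. The simulations used dyad totals with robust or clustered variance; neither the planned mixed model nor the mixed model recommended below was itself simulated.

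This is an inexpensive improvement to the plan, not an error in the planned test. It does not extend to the simulator outcomes.

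**What to change.** Keep the planned per-10-minute rates unchanged and prespecify one supporting contrast for the naturalistic drives:

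- Enter each drive's before-hazard and after-hazard HAC counts (after = total HAC minus before) as two rows in a mixed Poisson model. Use the same log-duration offset and covariates, with condition, timing, condition × timing, and dyad random effects for intercept and timing.
- Base any statement about earlier timing on condition × timing, reported as a ratio of rate ratios with its interval.
- Describe a raised before-hazard rate without that interaction as *more before-hazard HAC*, not *earlier HAC*.
- The same contrast for HAC with and without motivational interviewing is optional, and needed only if a change in style is to be claimed.

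The cost is a few lines of text and one model. Coding and analysis are still described in the future tense, and no new data are needed. There are three downsides. The contrast is less precise if HAC is rare. Only HACs that occur inform it: dyads without any stay in the model but add almost nothing, and a change in which hazards are discussed could shift it. It may also be null if the programme raises before- and after-hazard HAC equally, which would not count against the programme.
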